## Abstract

**Background:**

Anxiety, depression and stress-related conditions are prevalent and growing public health challenges, impacting individuals’ quality of life and placing significant strain on healthcare systems globally. These complex conditions rarely respond to a single mode of treatment, underscoring the importance of diverse and complementary approaches. Nature-based health interventions (NBHIs) represent one such perspective, offering novel opportunities to address mental health by engaging with natural environments. While international interest in NBHIs is growing, evidence on how these interventions can be systematically developed and implemented remains limited. The aim of this study protocol is to report the planned Nature Impact Feasibility Study.

**Methods:**

The Nature Impact Feasibility Study is a one-armed, mixed methods feasibility study aiming to evaluate a complex, group-based NBHI developed using the Medical Research Council framework for complex interventions. The intervention will be conducted across three sites in Denmark: Glostrup outpatient clinic, Kolding and Silkeborg municipality centres. The intervention consists of group-based NBHI programmes delivered weekly over 10 consecutive weeks, facilitated by experienced health professionals. The feasibility evaluation will examine three core domains. These include (1) the implementation process, including fidelity, dose, reach, adaptations and acceptability; (2) mechanisms of change and (3) contextual factors influencing implementation and intervention processes. Data will be collected through participant observations, focus group interviews, registration forms and participant questionnaires assessing mental health outcomes and the participants’ relationship to nature. Data will be analysed using a mixed methods convergent design. Quantitative and qualitative data will be analysed separately and then integrated thematically during interpretation.

**Discussion:**

By reporting the study protocol for the Nature Impact Feasibility Study in advance, the project enhances transparency, allows for critical appraisal of the planned design and methods and strengthens the foundation for the subsequent feasibility evaluation and future large-scale trials. The Nature Impact Feasibility Study will provide valuable insight into delivering NBHIs for adults experiencing mild to moderate anxiety, depression and/or stress, while informing intervention refinement, outcome measures and future research aimed at investigating the potential of integrating NBHIs into existing practices for treating anxiety, depression and stress.

**Trial registration:**

NCT06981000. Registered on March 13, 2025.

**Supplementary Information:**

The online version contains supplementary material available at https://doi.org/10.1186/s40814-026-01875-x.

## Background

Mental health problems constitute a world-wide growing public health concern, with significant implications for individuals, communities and the healthcare system [1]. According to the Global Burden of Disease Study 2021, the global age-standardised incidence rate (ASIR) of mental disorders reached 5456 per 100,000 individuals, representing a 15% increase since 1990. Anxiety and depression are the most prevalent contributors to this increase [1]. Despite this growing burden, mental health remains severely underfunded. Mental health receives, on average, only 2.1% of the national health budgets [2]. This underfunding limits the ability of healthcare systems to meet the growing and increasingly complex demands, particularly among patients who do not respond to standard treatments.

While clinical treatment and pharmacotherapy are essential components of mental healthcare, growing evidence indicates that these approaches can be insufficient. This is due not only to financial constraints, but also to the complex needs of patients who experience treatment resistance to standard pharmacological treatment [3, 4]. For example, a major review found that approximately one-third of individuals with depression do not respond adequately to standard pharmacological treatment [4]. This situation underscores the need for alternative and complementary approaches that can promote mental well-being and reduce the wider burden on healthcare systems.

One such approach gaining international attention is nature-based health interventions (NBHIs), which involve structured therapeutic engagement with natural environments. A growing body of research indicates that NBHIs can alleviate symptoms of anxiety, depression and stress [5–8]. However, despite international interest, there is a demand for a comprehensive, evidence-informed framework for the systematic development, implementation and evaluation of NBHIs in clinical and municipal healthcare settings [5–8]. To address this gap, a complex intervention development process is undertaken in the Nature Impact Feasibility Study, guided by the UK Medical Research Council’s (MRC) framework for developing and evaluating complex interventions [9]. This framework emphasises the importance of understanding not only the intervention and its outcomes but also the broader contextual factors that may influence implementation. Contextual factors refer to a broad range of conditions, e.g., organisational structures, participants’ mental health status, physical settings and weather conditions.

The present study protocol aims to report the planned Nature Impact Feasibility Study.

## The Nature Impact Feasibility Study

### Aim of the Nature Impact Feasibility Study

The primary aim of the Nature Impact Feasibility Study reported in this protocol is to evaluate the feasibility of the intervention. This will be done by examining three core domains: (1) the implementation process, including fidelity, dose, reach, adaptations and acceptability; (2) the mechanisms of change; and (3) contextual factors and how these influence the implementation and the mechanisms of change. The findings from this evaluation will provide a foundation for refining a programme theory and an intervention manual and guide the planning of future evaluation and effect studies.

The secondary aim of the Nature Impact Feasibility Study is to explore preliminary changes in participants’ mental health status during the intervention period, including mental well-being, symptoms of anxiety, depression and stress, life satisfaction and their connection to nature. This assessment aims to evaluate the suitability of the selected outcome measures and to provide insight into the intervention’s potential efficacy.

Building on the MRC framework [9], the Nature Impact Feasibility Study follows a structured approach consisting of two key phases: an initial intervention development phase and a subsequent feasibility testing phase, the latter of which is reported in detail in this protocol.

### Intervention development phase

The intervention development phase included several components. These comprised a systematic literature review on effects of NBHIs for individuals experiencing symptoms of mild to moderate anxiety, depression and/or stress [8], a narrative review of the mechanisms of change for NBHIs, stakeholder dialogue meetings, a Delphi survey with experts on group- and nature-based interventions [10]. In addition, a programme theory [11] and an intervention manual were developed to guide practitioners with NBHIs for future group- and nature-based interventions. The programme theory, presented through the logic model, outlines the relationships between the intervention’s inputs, core elements, mechanisms of change and anticipated outcomes. The model is intended as a flexible, practice-oriented tool to guide health professionals in the planning, delivery and evaluation of NBHIs. By allowing for contextual adaptation, the model has supported the design of interventions that are both evidence-informed and contextually appropriate.

The programme theory is informed by the Delphi process, which identified the following core mechanisms of change in NBHIs: nature interaction, social community and physical activity, alongside related processes such as sensory experiences, body awareness and self-reflection. These mechanisms have informed the design of the present intervention and are operationalised through group-based activities in natural environments, such as guided nature exposure, shared reflections and light physical group-activities, which are expected to support mental health through these interrelated processes. This is grounded in a bio-psycho-social approach.

Preparatory activities to support consistent delivery included workshops on co-creation and contextual adaptations, site visits, development of the intervention manual and competence development sessions across the three study sites (November 2024–March 2025).

Health professionals responsible for delivering the intervention have tailored the activities to suit the participants’ needs and resources using the potential of a specific natural environment. Potential risks have been assessed and minimised through the selection of suitable natural environments, appropriate equipment and thorough instructions.

Health professionals have been encouraged to create a safe, inclusive and supportive environment where participants can feel comfortable, both physically and psychologically. Accessibility and individual needs have been considered, to ensure that all participants can safely engage in the activities.

Figure 1 presents a detailed timeline of the intervention development and feasibility testing phases, encompassing all major project components. The indicated time frames for the articles refer to data collection only and does not include the writing process.

**Fig. 1 Fig1:**
[figure not shown]
Gantt chart displaying the timeline of the development and feasibility testing phases

## Methods

### Research design for the Nature Impact Feasibility Study

The feasibility study is designed with a one-armed, mixed methods, prospective design. As defined by Thabane and Lancaster, a feasibility study can inform the design of future main trials by assessing the feasibility and by identifying potential challenges [12]. A mixed methods convergent design [13] is used to pragmatically explore the feasibility parameters through qualitative and quantitative data, which are analysed separately and integrated thematically during interpretation. The design integrates quantitative and qualitative data to provide a comprehensive understanding of the feasibility and implementation in real-world settings. The domains, research questions and corresponding data collection methods are summarised in Table 1.

**Table 1 Tab1:** Table of domains, research questions and data collection methods

Domain	Research questions	Data collection
Implementation (dose)	What proportion of the scheduled sessions do participants attend?	-Post intervention participant questionnaires
Implementation (reach)	Who are the participants?	-Participant questionnaires -Participant registration forms -Focus group interviews with the participants -Participant observation
	Are the partners able to identify the right participants and does the intervention reach the intended target group?	-Focus group interviews with health professionals -Participant registration forms -Participant questionnaires -Participant observation
	Have any of the participants failed to complete the intervention (dropout) and what factors have contributed to their withdrawal?	-Focus group interviews with health professionals -Participant questionnaires
Implementation (fidelity)	Is the intervention delivered as planned, and how are its components put into practice?	-Participant observation -Focus group interviews with health professionals -Intervention registration form
Implementation (adaptation)	Which adaptations do the health professionals make to the content of the intervention and why?	-Intervention registration form -Focus group interviews with health professionals
	How does the local adjustments adhere to the programme theory?	-Participant observation -Focus group interviews with health professionals
Implementation (acceptability)	To what extent does the intervention match the participants’ functional ability and mentally condition?	-Participant observations -Focus group interviews with participants
	Are the purpose and content of the intervention clear to the participants and the health professionals?	-Participant observations -Focus group interviews with participants -Focus group interviews with health professionals
	To what extent do participants perceive the intervention as impactful?	-Focus group interviews with participants
	Are the professionals’ competencies aligned with the requirements of the intervention?	-Participant observations -Focus group interviews with health professionals
Mechanisms of change	Does the intervention function as intended and are the anticipated mechanisms of change activated as contributors to the observed outcomes?	-Participant observations -Intervention registration forms -Focus group interviews with health professionals -Focus group interviews with participants
Contextual factors	How do contextual factors influence the implementation of the intervention?	-Participant observations -Focus group interviews with health professionals -Focus group interviews with participants
	How do contextual factors influence the mechanisms of change?	-Participant observations -Focus group interviews with health professionals -Focus group interviews with participants
Mental health status	Have the participants experienced any changes in their mental health during the intervention?	-Participant questionnaires

The protocol has followed reporting guidelines for pilot and feasibility trials from Thabane and Lancaster [12] and follows the suggested utilisation of SPIRIT (Standard Protocol Items: Recommendations for Interventional Trials) [14], wherein some of the elements are replaced with elements from the CONSORT (The Consolidated Standards of Reporting Trials) [15] extension to pilot and feasibility trials. This combined approach is recommended because SPIRIT ensures completeness and structure, while the CONSORT extension tailors the focus to feasibility objectives such as recruitment, acceptability and trial procedures, which are more appropriate than definitive trial outcomes at this stage [12]. The adequately filled checklists for SPIRIT and CONSORT can be found in Additional files 1 and 2. Moreover, a SPIRIT figure, displaying a time schedule of enrolment, intervention and assessments, is displayed in Fig. 2.

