### The structure of the intervention

The NBHIs are structured as group-based programmes delivered over 10 consecutive weeks, with one weekly session. The interventions will be delivered between March and November 2025. The intervention will be rolled out in two consecutive rounds, each involving between two and three groups at each site. Each group consists of 8 to 12 participants in a closed group. The closed group format, where the participants attend the same group for the full duration of the programme, is intended to provide participation continuity and to support the development of trusting relationships and psychological safety. Sessions held in the municipality centres have a duration of two and a half hours, while those at the outpatient clinic have a duration of one and a half hours. 

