#### Participant questionnaires

Participants will be invited to complete two questionnaires assessing their mental health status and their relationship to nature using the validated instruments; WHO-5 Well-Being Index [19], Depression, Anxiety and Stress Scale (DASS-21) [20], Satisfaction with Life Scale (SWLS) [21] and Environmental Identity Scale [22]. These questionnaires are filled out pre- and post-intervention, right before the beginning of the first and at the end of the 10th session.

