#### Intervention registration forms

Throughout the intervention, health professionals will complete a session log after each session. This log records any deviations from the planned intervention content, including changes in session timing and location, alongside the reasons for these adjustments, e.g., weather conditions or participant needs and preferences.

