#### Quantitative data analysis

Quantitative data will primarily be derived from participant questionnaires and structured elements of the participant and the intervention registration forms.

The participant questionnaires will be analysed using descriptive statistics to inform the feasibility parameters dose and reach as well as secondary outcome measures related to changes in participants’ mental health and their relationship to nature as well as the relevance of the chosen mental health outcome measures. Descriptive analyses will include measures of central tendency and distribution, e.g. means, medians, standard deviations, for each timepoint, alongside pre and post comparisons to examine a potential change.

Data from the participant registration forms will be analysed descriptively to assess referral sources and reasons for non-participation, thereby informing the feasibility parameter reach.

Data from the intervention registration forms will be analysed descriptively to assess information on the feasibility parameters, fidelity and adaptations as well as mechanisms of change.

All the data will inform contextual factors.

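### The only source named for dose is a questionnaire completed at the end of session 10, so the attendance estimate approximates completers only and is biased upward

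*Protocol article*

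**What the plan says.** Dose is one of the implementation parameters under the primary aim. In Table 1 (Research design for the Nature Impact Feasibility Study) the dose question is "What proportion of the scheduled sessions do participants attend", and the data collection column has one entry: "Post intervention participant questionnaires". Several other rows of the table list three or four sources.

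The section Participant questionnaires says that these are filled out "right before the beginning of the first and at the end of the 10th session". The section Quantitative data analysis gives the same assignment: "The participant questionnaires will be analysed using descriptive statistics to inform the feasibility parameters dose and reach". The programme is "delivered over 10 consecutive weeks, with one weekly session", so ten sessions are scheduled.

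The other two forms are given different jobs. The participant registration form is completed before the intervention and covers referral and reasons for declining. The intervention registration form is completed after every session, and of it the article says: "This log records any deviations from the planned intervention content". Its analysis is assigned to fidelity, adaptations and mechanisms of change, not to dose.

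**The concern.** Being present at session 10 is part of what is being measured and is also the planned occasion for measuring it. Those who stopped coming, and those who missed the last session, are likely to be the lowest attenders. They drop out of both the numerator and the denominator. The result is then an attendance proportion among people who were still there at the end, while the question in Table 1 is about participants in general.

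The findings are meant to guide later evaluation and effect studies. A completers' figure read as the dose of everyone enrolled would give those studies too favourable a picture of attendance. Three parts of the article (Table 1, the questionnaire timing and the analysis section) agree on this arrangement. It is therefore a fixed choice and not a detail left to a fuller document.

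**Working it through.** **Inputs from the protocol article.** Ten scheduled sessions; a target of 120 participants; post questionnaire at the end of session 10; no other source assigned to dose. The article states no expected attendance or retention, so there is no planned figure to reproduce.

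**Step 1: direction.** Let r be the proportion retained, c the mean proportion of the ten sessions attended by completers, and d the same for drop-outs.

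- Dose over all enrolled = r·c + (1 − r)·d
- Dose from the questionnaire, if only completers answer = c
- Bias = c − [r·c + (1 − r)·d] = (1 − r)(c − d)

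This is positive whenever d < c and zero only if nobody drops out or drop-outs attend as much as completers.

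**Step 2: illustrative size.** Assume c = 0.90 and d between 0.20 and 0.40.

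| Drop-out (1 − r) | Dose over all enrolled | Questionnaire | Bias |
|---|---|---|---|
| 10% | 83–85% | 90% | 0.10 × (0.50 to 0.70) = 5–7 points |
| 20% | 76–80% | 90% | 0.20 × (0.50 to 0.70) = 10–14 points |
| 30% | 69–75% | 90% | 0.30 × (0.50 to 0.70) = 15–21 points |

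With a wider assumed range (c of 0.85–0.90, d of 0.10–0.50) the bias runs from 0.10 × (0.85 − 0.50) = 3.5 points at 90% retention to 0.30 × (0.90 − 0.10) = 24 points at 70% retention.

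**Step 3: absence at session 10 among people who did not drop out.** Step 2 assumes that every completer answers. If completers' individual attendance probabilities have mean m and standard deviation s, those present at session 10 have mean attendance [9(m² + s²)/m + 1]/10.

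- m = 0.85, s = 0.10: (9 × 0.8618 + 1)/10 = 0.876, an extra 2.6 points
- m = 0.80, s = 0.20: (9 × 0.85 + 1)/10 = 0.865, an extra 6.5 points

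Under these assumptions the number supplying a dose value is 120 × r × m: about 86–92 at 90% retention and 67–71 at 70%.

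**Step 4: could another described source fill the gap?** The participant registration form is completed before session 1. The session log covers content, timing and location. The article describes no attendance register and no contact with people absent at session 10.

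**The case against.** Five points can be made on the other side.

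- **Progression decision.** A reader might infer that the bias could move the study across a Go/Amend/Stop boundary, since Table 3 uses cut-offs of 90% and 70%. The documents do not support that. The adherence row, as worded, counts sessions carried out with only minor adaptations. That reads as delivery, and it puts no threshold on individual attendance. The legend links adherence to dose, so the matter is not wholly closed, but no shift can be claimed. This objection stands.
- **Drop-out is visible elsewhere.** Retention has its own criterion in Table 3. In the 20% and 30% drop-out illustrations, retention of 80% or 70% already falls in the Amend band, whatever the questionnaire shows. This limits the harm, but it does not correct the dose figure.
- **Remote completion.** It would be too strong to say that only people present at session 10 can answer. Under Ethical considerations, access is by QR code to a digital platform, so an absentee could respond. No procedure for this is described, however, and the stated timing is the end of session 10. Hence *mostly missing*, not *all missing*.
- **The forms are not shown.** The article summarises the session log in two sentences and mentions structured elements of the forms without listing them. A headcount may exist in practice. Even so, the article does not assign it to dose. The attendance item in the questionnaire is not shown either, so nothing firm can be said about recall error.
- **Hours.** A reader might add that full attendance means 10 × 2.5 = 25 hours at the municipality centres and 10 × 1.5 = 15 hours at the clinic. The session lengths are stated openly ("Sessions held in the municipality centres have a duration of two and a half hours" for the municipalities) and dose is defined in sessions. This is a reporting preference, not an error.

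**Conclusion.** The point holds for the dose estimate itself. As planned, it will approximate attendance among people present at session 10 and will overstate attendance among all enrolled. The direction rests on one mild assumption, that drop-outs and session-10 absentees attended fewer sessions than those who answered. The size cannot be derived from the documents. The 5–7 points at 10% drop-out and 15–21 points at 30% are illustrations that depend on the assumed 90% and 20–40% attendance.

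The weakness affects one descriptive parameter of the primary aim that has no explicit progression threshold of its own. It should be fixed, but it does not undermine the study as a whole.

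**What to change.** In Table 1, make the intervention registration form the source for dose and add attendance to it for each session. This can be the number enrolled and the number present in each group, or a tick per participant. A headcount is enough for the mean; ticks also give the spread across participants. Define

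dose = total attendances / (10 × all enrolled participants),

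with drop-outs counted as absent after they leave, and report it by site. Amend the sentence in Quantitative data analysis to match. Keep the questionnaire item as a cross-check at group or site level, because the article states that no key links questionnaire codes to persons.

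Delivery was scheduled for March to November 2025. If it is complete, use site attendance lists where they exist. Otherwise label the questionnaire figure as completers only, state how many of those enrolled it covers, and report it beside retention.

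The cost is a small addition to a form already completed after every session, and a reported dose that will probably be lower.
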